**Figure 2 F2:**
[figure not shown]
**Algorithm for pain medication.** The left side shows the algorithm for medication when the patient has nociceptive pain. The right side shows the algorithm for medication when the patient has neuropathic pain. In case of mixed pain, a switch can be done as indicated.

**Figure 3 F3:**
[figure not shown]
Algorithm for antidepressant medication.

The detailed content of the collaborative care intervention is described below:

1. *Diagnostic assessment of the nature of pain symptoms*

The nature and the extent of the pain symptoms will be explored by the psychiatrist with the BPI and the painDETECT [74]. The 'average pain' item from the BPI will be used to assess the severity of the pain symptoms. To identify the pain symptoms as nociceptive and/or neuropathic, the painDETECT will be used. Because a patient can have both neuropathic pain and nociceptive pain at the same time, our pain medication protocol has been edited accordingly. Chronic pain may be a function of a chronic underlying pathology that appears within 4 to 6 weeks of an initial trauma; however, in accordance with the use of the terms chronic and subchronic pain in musculoskeletal pain or back pain, we apply the terms chronic and subchronic as follows: We define subchronic pain as pain with at least 6 weeks and less than 12 weeks duration, and chronic pain as pain of ≥ 12 weeks duration [6].

2. *Contracting*

During the initial visit, the care-manager informs the patient about the depressive disorder and pain symptoms, and their association. The treatment plan is then jointly formulated by the psychiatrist, the care-manager and the patient.

3. *Pain medication protocol*

In this study, pain is divided in nociceptive pain and neuropathic pain and treatment of pain will be applied based on which of these two sorts of pain a patient has. Classification as nociceptive pain, neuropathic pain or mixed pain will be done with the PainDETECT questionnaire that was specifically validated for this purpose [74].

In all instances, patients are urged to take the medication at preset intervals, in order to medicate properly so as to prevent serious pain. In all instances, duloxetine (or placebo) is prescribed as adjuvant.

The psychiatrist will use the painDETECT questionnaire to identify the pain as nociceptive or neuropathic. When it is not clear in which of these two categories the pain belongs, both the algorithms for nociceptive and for neuropathic pain are followed. The algorithm for nociceptive pain, is adapted and changed from the WHO pain ladder [80]. It is updated for the use of selective Coxinhibitors, the role of so-called adjuvants is more prominent here; the role of opioids is much less prominent, but the principle of adding medication that is common in the WHO pain ladder, is maintained. This algorithm has been developed by the research group and was tested for feasibility in patients with mental disorder in a prepilot of this trial.

Figure 2 shows a graphical version of above mentioned algorithm.

When, after 12 weeks, the patient is referred back to the GP, the GP is advised, through a Consultation Letter, to continue the medication for a duration of 6 months, as is advised in the 'NHG standard – depression' [81], a guideline for general practitioners. The GP will monitor pain symptoms with the BPI during a consult, every 6 weeks.

4. *Manual guided self-help for behavioral techniques aimed at improving coping with pain*

During the treatment, the patient works through a self-help manual, guided by the care-manager. The manual is based on several existing self-help books [43-46]. This self-help book contains information about depression and pain symptoms and their interaction, antidepressant medication, relaxation techniques and a diary for pain complaints. Every chapter contains exercises for the patients to perform. The care-manager informs the patient about the content of the manual, reinforces achievements and motivates the patient to continue. In the present study, the self-help manual is part of a complete intervention package and is therefore meant as additional to the other components of the intervention.

5. *Problem Solving Treatment*

Problem Solving Treatment (PST) is a brief, structured psychological intervention, guided by the care-manager, that has been shown to be effective in the management of depressive disorders and stress related disorders [82]. The problem-solving approach consists of 7 stages and is based on the common observation that emotional symptoms are often associated with problems in daily life and it encourages patients to formulate practical ways of dealing with such problems. The goal of PST is to teach patients to use their own skills and resources to function better [82,83], thus improving coping skills.

6. *Antidepressant medication*

In the two collaborative care conditions, patients will either receive duloxetine or placebo in a double blind fashion. The psychiatrist will monitor medication use according to protocol. In case of any adverse effects, an adverse effects protocol is followed. The pharmacists checks for possible interactions of the antidepressant medication with other medication use of the patient and instructs the doctors providing treatment accordingly.

Patients will start with a dose of 30 mg once daily in the first two weeks and 60 mg once daily from the third week. From this point the PHQ-9 will be used to measure the severity of depressive symptoms. Based on the score on the PHQ-9, the dose will be raised (when the score did not decrease; with a maximum of 90 mg) or stay the same (when the score on the PHQ-9 has decreased with 5 or more points or the score on the PHQ-9 is 5 or lower). This use of the PHQ9 for monitoring was used as well in other collaborative care studies in the Netherlands, with a focus on depression [84-87]. By using the PHQ9, comparisons can also be made with these studies. After 12 weeks the randomization code will be broken and medication will be prescribed if necessary in a standard continuation phase of at least six months. Pharmacotherapy will be gradually discontinued according to protocol and/or clinicians judgment. When the patient is referred back to the GP, the GP is advised, through a Consultation Letter, to continue duloxetine for the duration of 6 months. After this period, if possible, the GP reduces and stops the use of duloxetine in a period of 4 weeks. In case of placebo, the GP is advised to only prescribe medication when the patient still has depressive symptoms. Figure 3 shows the graphical version of the abovementioned algorithm.

7. *Monitoring treatment outcome and motivational techniques aimed at improving adherence*

Patient adherence will be improved by contracting and psycho-education and by frequent follow-up appointments in which both adherence and progress will be evaluated. Provider adherence will be improved by instructions from the researchers. Treatment outcome is monitored with a variety of questionnaires (see section 'Outcome parameters').

8. *Referral to the physiotherapist by the care-manager according to a protocol*

Next to manual guided self-help, Problem Solving Treatment and medication, patients receive physiotherapy. The physiotherapist will treat patients according to the protocol of 'graded activity'. This treatment consists of information of physical and psychological processes and how these can be intertwined. The next step is to formulate reasonable goals on what to achieve with this therapy. According to these goals, intermediate steps are formulated that have to take into account the amount of time that is predetermined.

The physiotherapist stimulates the patients with positive feedback. Also, the therapist works on a structured time schedule to optimize the course towards the determined goals. Next to the exercises, the therapist pays attention to the progress of the patients. This will be illustrated by graphs and when positive, these serve as a possible positive reinforcer and can motivate the patient.

The patients also conducts the exercises at home, so these exercises generalize to situations the patients live in. In this, the patients are stimulated by their physiotherapist.

9. *Consultation Letter*

The consultation letter is written by the psychiatrist and is meant for the GP and the patient. In this letter, the symptoms of the patient are described (somatic and psychological). This letter will also contain the treatment the patient has received in this study, as well as if the patient improved or not. The expected course of the complaints will be described, and with this an advice is given how to continue treatment of the patient by the GP. An advice is given for continuing medication (antidepressants and pain medication), the number of regularly scheduled consults with the patient every 6 weeks as checkup, to perform only physical examination if the patient presents the same symptoms again, and refrain from repeated lab or diagnostic procedures as well as to avoid hospitalization, as long as the patient does not deteriorate or presents with new symptoms. Also, the GP can consult the psychiatrist if needed. This consultation letter is sent 3 months after start of treatment, when the patient is referred back to the GP.

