### Deblinding

After 12 weeks, the placebo-controlled part of the study will end and the patient and physician will be deblinded for this part of the intervention. This deblinding procedure is described more detailed in the intervention.

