#### Intervention

##### First and second design arm: Duloxetine/placebo plus collaborative care

This intervention contains collaborative care, duloxetine or placebo, and pain medication according to an algorithm. Collaborative care will be provided within a multidisciplinary team comprising of a care-manager, psychiatrist and a physiotherapist. They all will apply treatment simultaneously according to protocol. Only patients in the collaborative care arms will receive treatment of all three specialists. The patients in the Duloxetine alone arm will only receive treatment of the psychiatrist.

The GP of the patient will be informed of the participating of the patient. Also, GP's in the same areas as the mental health centers will receive information about the study and are asked to refer patients if they have the complaints under study. The interventions will be monitored every two weeks and when needed, the doses of medication can be raised according to the algorithm shown in Figures 2 and 3. The minimum duration of the interventions will be 12 weeks. The medication blinding code will be broken after 12 weeks. A maximum of 2 sessions will follow to end the treatment. After this, medication and follow up treatment will be handed over to the GP. In case of treatment response (50% reduction on the initial score), but non-remission, as indicated by a score of > 5 on the PHQ-9 after 12 weeks, the patient will be referred back to the GP with subsequent antidepressant treatment and pain medication advice.

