#### Data collection

Measurement will take place at baseline (T0), and three, six, nine and twelve months after baseline, respectively T1, T2, T3 and T4.

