#### Primary outcome parameter

Primary parameter used to substantiate the study hypothesis will be severity of depression (PHQ-9) [13]. The severity of depressive symptoms is measured with the Patient Health Questionnaire depression sub-scale [13], a brief but validated instrument that scores each of the DSM-IV criteria for major depressive disorder. Response is defined as a 50% reduction in symptoms [13,39,88]. Remission is defined as < 5 points on the PHQ-9 [88].

2. *Secondary outcome measure*

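### The primary duloxetine-placebo contrast has no PHQ-9 time point, nothing places T1 before the 12-week code break, and T2 to T4 all come after it

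*Protocol article*

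**What the plan says.** The Objectives and Hypothesis sections of the protocol article compare collaborative care plus duloxetine with collaborative care plus placebo, and with duloxetine alone, on PHQ-9 severity. The Analysis section makes the duloxetine-placebo comparison the second Helmert contrast in a multilevel analysis. Neither these sections nor Primary outcome parameter says at which follow-up the PHQ-9 is compared.

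On the end of blinding, the Deblinding section says: "After 12 weeks, the placebo-controlled part of the study will end and the patient and physician will be deblinded for this part of the intervention". The Intervention section repeats it: "The medication blinding code will be broken after 12 weeks". Item 6 (Antidepressant medication) adds what follows: "After 12 weeks the randomization code will be broken and medication will be prescribed if necessary". Patients found to have had duloxetine are handed to the GP with advice to continue it for six months. For the others: "In case of placebo, the GP is advised to only prescribe medication when the patient still has depressive symptoms".

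On outcome timing, Data collection says: "Measurement will take place at baseline (T0), and three, six, nine and twelve months after baseline". These visits are labelled T1 to T4. Recruitment of patients places completion of the baseline questionnaire before randomisation. Item 9 (Consultation Letter) counts three months from the start of treatment.

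Treatment allocation and blinding describes medication within collaborative care as double blind and placebo controlled, with outcomes assessed by a blinded research assistant.

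**The concern.** The placebo arm exists to isolate the effect of duloxetine when collaborative care is already given; the Discussion counts this among the strengths of the design. That reading needs outcomes recorded while patient and psychiatrist do not know the allocation and while the arms still differ as randomised.

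The plan secures neither condition for the analysed PHQ-9. A patient who has just learned that the capsules were placebo may rate mood differently from one who has just learned they were duloxetine. From then on, one arm is advised to continue a known antidepressant, and the other may be prescribed medication because of its own poor outcome. The first problem can bias the contrast in either direction; the second would tend to shrink it. A contrast with no time point leaves open whether these later data enter the primary result.

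The stakes are highest at T1, the only follow-up that can be blinded. A questionnaire answered after disclosure cannot be made blind again by any later analysis.

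**Working it through.** **1. The two clocks.** Inputs: code break at 12 weeks (Deblinding; Intervention; item 6); T1 to T4 at 3, 6, 9 and 12 months from baseline (Data collection); baseline before randomisation (Recruitment of patients). I take a month as 365.25/12 days.

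- Code break: 12 × 7 = 84 days from the start of treatment.
- T1: 365.25/4 = 91.3 days from baseline.
- Let g be the number of days from baseline to the start of treatment. T1 precedes the code break when 91.3 < g + 84, that is, when g > 7.3 days.
- T2 is at 182.6 days, so it would precede the code break only if g > 98.6 days (about 14 weeks). Nothing in the article suggests such a delay. T3 (273.9 days) and T4 (365.25 days) are later still.

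The article gives no value or limit for g, and no sentence requires T1 to be completed before the code is opened. The order at T1 is therefore left to scheduling, and three of four follow-ups (75%) are open-label.

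**2. The plan's own sample size.** Sample size gives 63 completers per arm for a standardised difference of 0.5 with 80% power. Assuming two-sided alpha 0.05, which is not stated:

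- n = 2 × (1.960 + 0.842)² / 0.5² = 62.8, so 63. Power at 63 per arm is 80.1%. The figure reproduces, and the timing problem does not alter it.

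**3. Why no loss of power can be derived.** Suppose, only for illustration, that the effect is 0.5 SD at T1 and d₂ at T2 to T4, that the four follow-ups are averaged with equal weight, and that the within-patient correlation is ρ. Neither the averaging, d₂ nor ρ is in the article.

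- Mean effect = (0.5 + 3d₂)/4.
- Variance of the mean of four = (1 + 3ρ)/4, which is 0.775 for ρ = 0.7 and 0.625 for ρ = 0.5.
- Power = Φ(mean effect / √variance × √(63/2) − 1.96).

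| Assumed d₂ | Mean effect | Power, ρ = 0.7 | Power, ρ = 0.5 |
|---|---|---|---|
| 0.5 | 0.500 | 89% | 94% |
| 0.3 | 0.350 | 61% | 70% |
| 0.2 | 0.275 | 42% | 50% |
| 0.1 | 0.200 | 25% | 29% |

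For example, with d₂ = 0.2 and ρ = 0.5: 0.275/√0.625 = 0.348; 0.348 × 5.612 = 1.95; Φ(1.95 − 1.96) is about 50%. The range runs from better than planned to far worse, and the documents do not say where in it the trial would fall.

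**The case against.** The strongest reply is that the code break is planned and openly described, and that the article never claims a blinded comparison at six to twelve months. It also uses 12 weeks and three months for the same moment, the referral back to the GP (compare items 3 and 9 of the Intervention section), so T1 is evidently meant as the end-of-treatment assessment. The baseline questionnaire comes first, and randomisation and appointments follow, so a gap of more than a week is plausible and T1 would then be blinded. The time point and the time structure of the model belong in an analysis plan that is not shown.

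Much of this stands. A reader might infer that T1 is always unblinded; the documents do not support that, because its order relative to the code break depends on an unstated delay. A reader might also infer that the trial is underpowered; that rests on assumed later effects and on an average of T1 to T4 that the article does not prescribe. The Analysis section gives site variance as the reason for the multilevel model, and an estimate at T1 from such a model would fit it equally well.

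The reply does not remove the core. An analysis plan can choose T1, but it cannot restore blinding to a T1 questionnaire completed after disclosure; that order is a matter of trial conduct. The blinded research assistant does not help, since the article describes the PHQ-9 as a questionnaire and the patient is among those deblinded. The authors themselves treat unblinding as serious: Emergency deblinding removes from the final analysis anyone deblinded before treatment procedures end.

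**Conclusion.** The concern holds in this form: the duloxetine-placebo contrast is part of the primary objective, its PHQ-9 time point is not named, nothing secures T1 as blinded, and T2 to T4 follow disclosure and outcome-dependent prescribing. T1 is possibly, not certainly, unblinded; the threshold is a delay of about seven days from baseline to treatment start, if the 12 weeks run from treatment start.

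The size of any bias or dilution cannot be derived from the documents, and the power figures above should not be cited as a finding.

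It would also go too far to conclude that T1 must be primary for the whole trial. The comparison of duloxetine alone with the collaborative care arms is non-blind by design, so the code break gives no reason to fix or change its time point.

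**What to change.** For the duloxetine-placebo contrast only:

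- Name the T1 PHQ-9 as the primary time point.
- Require the T1 questionnaire to be completed before that patient's code is opened at the planned end of the blinded phase, and record both dates. Emergency deblinding is not affected.
- Take the arm difference at T1 from the planned multilevel model as the primary estimate.
- Report T2 to T4 as open-label follow-up of treatment strategies, and describe antidepressant use after the code break in each arm.

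State one time origin for the code break, the consultation letter and the outcome visits, so that Deblinding, Intervention (including items 6 and 9) and Data collection agree. State the time point for the contrast with duloxetine alone separately. None of this says when or what treatment should be given; that remains with the investigators.

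The cost is modest but not nil. Results at 6 to 12 months become secondary for this contrast, and opening the code waits for the T1 questionnaire, which adds a dependency at handover. No assessment is added. If T1 is moved while T2 to T4 stay on the baseline clock, the even three-month spacing is lost; since the TiC-P asks about care in the last three months, the cost data could then have gaps or overlaps. Moving all follow-ups to the same origin avoids this among T1 to T4.

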### Third design arm: duloxetine alone

In the Duloxetine alone condition, patients will receive duloxetine according to the algorithm as described on page 10 (*6. Antidepressant medication*). No other components, i.e. PST, manual guided self-help, pain medication, physiotherapy, and a consultation letter, of collaborative care will be given here. Patients in this condition will only be prescribed Duloxetine by a psychiatrist.

#### Data collection

Measurement will take place at baseline (T0), and three, six, nine and twelve months after baseline, respectively T1, T2, T3 and T4.

#### Outcome parameters

1. *Primary outcome measure*

#### Primary outcome parameter

Primary parameter used to substantiate the study hypothesis will be severity of depression (PHQ-9) [13]. The severity of depressive symptoms is measured with the Patient Health Questionnaire depression sub-scale [13], a brief but validated instrument that scores each of the DSM-IV criteria for major depressive disorder. Response is defined as a 50% reduction in symptoms [13,39,88]. Remission is defined as < 5 points on the PHQ-9 [88].

2. *Secondary outcome measure*

#### Secondary parameters

Secondary parameter will be the severity of pain symptoms as measured with the total BPI. The BPI has been validated for chronic non-malignant pain [79]. The localization of pain and pain being nociceptive, neuropathic or mixed of nature is assessed at the beginning of the treatment by use of the PAINDETECT questionnaire [74].

In addition to the improvement in the severity of symptoms, the cost utility of the three conditions will be compared to each other. To evaluate the cost utility of each condition, the difference in direct medical costs per patient receiving collaborative care and duloxetine, collaborative care and placebo, or Duloxetine alone is related to the difference in terms of Quality Adjusted Life Years (QALY) gained. This will yield a cost per QALY estimate. These data will be collected with the Trimbos/iMTA questionnaire for Costs associated with Psychiatric Illness (TiC-P), a measure commonly applied in economic evaluations of treatment in mental care [89,90]. The TiC-P measures direct costs of medical treatment such as the number of contacts with the general practitioner and multiple other care providers (e.g. paramedics and medical specialists) during the last three months. Medication use is measured during the last four weeks. Also, the TiC-P includes a short form of the Health and Labor questionnaire (HLQ) for collecting data on productivity losses [91], the SF-HLQ. It measures productivity loss by collecting data on absence from work, reduced efficiency at work and difficulties with job performance [92].

The EuroQoL (EQ-5D) [93] and the Short Form-36 (SF-36) [94] will be used to assess quality of life. Both are validated instruments for the measurement of general health-related quality of life. The EQ-5D measures quality of life on five dimensions, namely mobility, self-care, usual activities, pain/discomfort and anxiety depression.

3. *Additional outcome measures*

Confusion exists in terminology in describing physical symptoms and pain associated with depression [5,95]: They may be somatised symptoms of MDD, or so-called associated symptoms [96]; Medically Unexplained Symptoms, that frequently occur together with MDD [97]; chronic painful physical conditions that are symptoms of a chronic illness, such as diabetic neuropathy; or chronic painful conditions resulting from centralisation of a formerly peripheral pain symptom [63]. In this study, we use the psychiatrist's professional view on whether what kind of physical symptoms a patient has. Comorbid mental disorders will be assessed with the PHQ and GAD7 [98]. Hypochondriac tendencies will be measured using the Whitely Index [99]. The Patient-Doctor relationship Questionnaire (PDRQ-9) [100] will be used to measure the patient doctor relationship from the perspective of the patient. Physical symptoms are measured by the Physical Symptoms Questionnaire (LKV: Lichamelijke Klachten Vragenlijst) [101]. The Morisky Medication Adherence Scale (MMAS) [102] will be used to measure pain medication adherence. The questionnaire TiC-P (‘vragenlijst voor zorggebruik en productieverliezen bij psychische aandoeningen') [89] will be used to assess provided health care. To measure coping in stressful situations, the 'Coping Inventory for Stressful Situations (CISS) [103], Dutch version, will be used. To measure the tendency to overload, the 'Tendency to Overload Questionnaire' (TOQ) short form will be used [in press].

4. *Controlling variables*

The following demographic variables are measured at baseline and will be taken into account as possible effect modifiers: age, gender, nationality and ethnicity, marital status, living conditions, education and work status. Also, pain classification (neuropathic, nociceptive, subchronic, chronic) will be taken as effect modifier. Moreover, existing somatic comorbidity will be taken as effect modifier. Co-morbid chronic medical illness will be measured with the Dutch Central Bureau for Statistics list (CBS list). The list contains 28 chronic conditions (e.g. diabetes and MS).

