#### Recruitment of patients

All the patients that are referred to the participating mental health centers are screened for depressive symptoms and pain complaints. This study will focus on patients with a depressive disorder and (sub)chronic pain complaints. Sub chronic pain is defined as pain of ≥ 6 weeks and chronic pain is defined as pain with a duration of at least 12 weeks. Consecutive patients that present themselves at the special mental health outpatient clinic will be screened for MDD and concomitant pain of ≥ 6 weeks duration with a questionnaire.

This questionnaire will consist of the PHQ-9 [13] and the item on 'average pain' from the BPI [79], that will be used as a screener for respectively depressive disorder and (sub)chronic pain symptoms. Also, the patient will receive an informed consent form with information about the study. Patients are eligible for the study if they have a score of 10 or more on the PHQ-9 and a score of 3 or more on the 'average pain' item of the BPI. When a patient screens positive on the questionnaires mentioned above, the patient will receive a telephonic interview in which a MINI interview will be administered in order to clinically confirm the diagnosis MDD and to confirm that the patient suffers from (sub)chronic pain. In that case, he or she will receive additional information about the treatment part of the study and will be asked if he or she is willing to participate. When the patient is willing to participate, the patient is included in the study. A baseline questionnaire with second informed consent form, for the treatment part of the study, will be sent to the patient’s home address or made available on a secured website. After completion of the baseline questionnaire, the patient will be randomized in one of the three interventions.

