## Discussion

This paper describes the study protocol of a Multi-Center randomized controlled trial evaluating collaborative care, antidepressant medication and pain medication in the treatment of depressive disorders with (sub)chronic pain. The aim of this study is to compare three treatments in terms of (cost)effectiveness.

A strength of this study is that the three arm design enables us to show the value of a closely monitored integrated treatment model above usual pharmacological treatment. Another strength of the study is that the comparison with a placebo arm enables us to evaluate effectiveness of duloxetine in this population in a real life setting.

Also, a strong aspect of this design is that this will provide evidence-based treatments and tools for their implementation in practice. This will facilitate generalization and implementation of results of this study.

Furthermore, patients included in this study are screened for pain symptoms, differentiating between nociceptive and neuropathic pain, unlike the studies of Goldstein et al. [107]. Therefore, pain relief can be thoroughly evaluated.

Another strength of the study is the structured implementation of a transmural model, aimed at better collaboration between GP and specialty mental health clinic in complex patients with depression and concomitant (sub)chronic pain.

A limitation of the study is that, with this study design, we will not be able to make inferences about the effectiveness of the respective ingredients of the collaborative care model (such as PST or the self-help manual).

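### Pain type is a trial-wide effect modifier, but painDETECT is placed after randomisation and the text conflicts on whether the duloxetine-alone arm receives it

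*Protocol article*

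**What the plan says.** The sub-section on controlling variables, under Outcome parameters, states: "Also, pain classification (neuropathic, nociceptive, subchronic, chronic) will be taken as effect modifier". It limits this to no arm.

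On timing, Secondary parameters says that the nature of the pain "is assessed at the beginning of the treatment by use of the PAINDETECT questionnaire". Recruitment of patients gives the order of events before that: "After completion of the baseline questionnaire, the patient will be randomized in one of the three interventions". The screener used earlier is short: "This questionnaire will consist of the PHQ-9 [13] and the item on 'average pain' from the BPI". A telephone interview follows, with a MINI to establish the depression diagnosis and "to confirm that the patient suffers from (sub)chronic pain". No step described before randomisation separates nociceptive from neuropathic pain.

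On who does it and where, the first item in the detailed description of collaborative care reads: "The nature and the extent of the pain symptoms will be explored by the psychiatrist with the BPI and the painDETECT". The Background subsection defining (sub)chronic pain also introduces the classification as part of pain-medication management in collaborative care. The section on the third design arm refers only to the antidepressant algorithm, lists components that are not given, and closes: "Patients in this condition will only be prescribed Duloxetine by a psychiatrist".

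The Discussion, in line with the Abstract, counts it as an asset that "patients included in this study are screened for pain symptoms, differentiating between nociceptive and neuropathic pain".

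**The concern.** An effect modifier is safest when it is recorded before allocation, in the same way, in every arm that enters the comparison. Here the described order puts pain type after allocation, in the hands of a treating clinician. Treatment allocation and blinding says that collaborative care and duloxetine alone are given openly, so for that comparison the person recording the modifier knows the arm. In collaborative care the result also decides which branch of the pain-medication algorithm is followed; in the duloxetine-alone arm it has no such use, because pain medication is not managed there. Sites therefore have a practical reason to complete painDETECT in two arms and none to complete it in the third.

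What is at stake is whether the effect of collaborative care differs by pain type, and whether the trial can describe its whole population by pain type, as the Abstract and Discussion suggest.

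**Working it through.** **Arm size.** Sample size gives 63 completers per arm for a standardised difference of 0.5 at 80% power. Assuming two-sided alpha of 0.05 (not stated there), n = 2 × (1.96 + 0.8416)² / 0.5² = 62.8, so 63. Allowing for 20% loss, 63 / 0.80 = 78.75, so 79 per arm and 3 × 79 = 237. The plan's figures are reproduced. The 73 in Study design is a target per institution and is not used here as an arm size.

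**Timing.**
1. Screening: PHQ-9 and one BPI item.
2. Telephone interview: MINI, and confirmation that (sub)chronic pain is present.
3. Baseline questionnaire, by post or secured website.
4. Randomisation.
5. Start of treatment, where Secondary parameters places painDETECT.

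As written, pain type is therefore a post-randomisation record. Duration is better placed: step 2 confirms that the pain qualifies. But the text does not say that subchronic versus chronic status is recorded at that step, and that split is part of the named modifier.

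**Arm coverage, side by side.**
- For all arms: Secondary parameters has no arm restriction; the Abstract and Discussion speak of patients included in the study; the list of withheld components in the third-arm section does not mention pain assessment.
- For collaborative care only: the procedure appears as item 1 of the collaborative care content; its stated purpose is to steer pain medication, which the third arm does not receive; the third-arm section limits that arm to a prescription. The withheld list also leaves out contracting, which is item 2 of collaborative care, so absence from the list does not show that something is given.

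The two sets cannot both be followed.

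**Consequence for the contrasts in Analysis.** Let d_a, d_b and d_c be the difference in mean PHQ-9 between neuropathic and nociceptive patients under collaborative care with duloxetine, collaborative care with placebo, and duloxetine alone.
- Modification of the first Helmert contrast (duloxetine alone versus both collaborative care arms): (d_a + d_b)/2 − d_c.
- Modification of the second (duloxetine versus placebo within collaborative care): d_a − d_b.

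If painDETECT is done only in collaborative care, d_c has no data. Pain type is then missing for 79/237 = 33.3% of patients (63/189 = 33.3% of completers). The first quantity cannot be estimated; the second can.

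If painDETECT is done in all arms at the first treatment session, all three terms have data, but only from patients who attend. The number lost between randomisation and that session is not given, so this loss cannot be sized.

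**Primary analysis.** The covariates named in Analysis are age, gender, immigrant status, education, treatment history and life events. Pain type is not among them, so the main contrasts do not depend on it.

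**The case against.** The strongest reply is that the article never says the duloxetine-alone arm goes without painDETECT. The sentence in Secondary parameters applies on its face to everyone, and the closing sentence on the third arm contrasts treatments, not measurements. Read literally, it would also rule out the PHQ-9 dose monitoring, pill counts and side-effect checklist that the protocol describes for psychiatrist sessions. This stands. A reader might infer that one arm is certainly left unclassified; the documents show a contradiction, not an absence.

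Second, a reader might take the psychiatrist to be fully aware of the arm. That is wrong for duloxetine versus placebo, to which psychiatrists are blinded, and classification is by a validated questionnaire, not free opinion.

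Third, a class recorded at the very start of treatment has little time to be changed by it. That also stands: late recording does not make the variable unusable. The remaining risk is missing or unequal assessment between the open arms.

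Fourth, the Abstract and Discussion promise a thorough evaluation of pain relief, not one by pain type. Pain severity is measured with the BPI, without arm restriction, so that promise does not fail on this point.

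Finally, an article condenses. The content of the baseline questionnaire is not listed and the case registration form is not shown. This does not dispose of the matter, because the article does state a time, an assessor and a place in the intervention, and those conflict with the role given to pain type.

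**Conclusion.** The point holds in a limited form. Pain type, a trial-wide effect modifier, is placed after randomisation and described operationally only within collaborative care; coverage of the duloxetine-alone arm is inconsistent.

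The size depends on which text sites follow. Under the intervention sections, one third of patients lack a pain type and its modification of the first Helmert contrast is not estimable. This assumes equal arms, as the sample size implies. Under the outcome section, the loss is confined to patients who do not start treatment, possibly unequally between openly allocated arms, and is of unknown size. Under either, modification of the duloxetine-placebo contrast remains estimable and blinded.

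It would go too far to conclude that pain type cannot serve as a modifier in this trial; it is not secured as written. The primary analysis and sample size are untouched. The change is worth making because it is cheap, but it is not critical.

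**What to change.** Include painDETECT, which the protocol itself calls a questionnaire, in the baseline (T0) package for all three arms, completed before randomisation. Record there whether pain is subchronic or chronic, since the interview is said only to confirm that qualifying pain is present. State that the T0 class is the one used in the effect-modifier analysis. Use of the result in the collaborative care arms need not change.

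If patients have already been randomised without it, restrict the pain-type modifier analysis to the two collaborative care arms and say so.

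In either case, reconcile Secondary parameters, the collaborative care description and the third-arm section on who is classified, and align the Abstract and Discussion with when and in whom pain type is actually determined.

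The cost is one more questionnaire in a package already sent by post or web: a small added burden for patients, with no extra visit or staff.
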